**Protocol Synopsis**

| **Title:** | Role of Pioglitazone and Berberine in the Treatment of Non-alcoholic Fatty Liver Disease(NAFLD) Patients With Impaired Glucose Regulation or Type 2 Diabetes Mellitus |
| --- | --- |
| **Primary Objective:** | To assess the effects and safety of pioglitazone (15mg daily), a thiazolidinedione insulin sensitizer, and Berberine (BBR), a component isolated from a Chinese herb, on hepatic fat content and glucose and lipid metabolism in NAFLD patients with impaired glucose regulation (IGR) or T2DM. |
| **Study Design:** | The study is a three-center, randomized, parallel controlled, open clinical trial of treatment with pioglitazone, berberine or no drug on the basis of life style intervention for NAFLD patients with IGR or T2DM. The screening period for evaluating eligibility and collecting baseline data lasted up to 4 weeks before randomization. Eligible patients were randomized to receive pioglitazone (15 mg q.d), berberine (0.5g t.i.d.) or no-drug on basis of Life style intervention for 16 weeks. The primary comparison will be made using an intention-to-treat analysis of the change in OGTT (glucose, insulin, AUC of glucose), HbA1c; lipid profile（TC, TG, HDL-c, LDL-c, ApoA, ApoB, ApoE, Lpa); liver enzymes (ALT, AST, γ-GT, ALP). The secondary outcome is liver fat content by 1H NMR spectroscopy. |
| **Patient Population:** | Patients aged 18 to 65 years with fatty liver (Hepatic fat content assessed by ^1^H MRS were no less than 13%) and impaired glucose metabolism were enrolled. |
| **Inclusion Criteria:** | 1.Patients must have an age range between 18 to 65 years(inclusive).  2. Patients with Liver fat content assessed by 1H MRS≥13%.  3. Patients must meet the criteria for impaired glucose regulation or type 2 diabetes mellitus(FPG≥5.6mmol/L and/or a two hour glucose value≥7.8mmol/L) .Patients with a HbA1c＞7.5% will be excluded from the study.  4.Course of diabetic mellitus less than 1 year |
| **Exclusion Criteria:** | 1.Any causes of chronic liver disease other than NAFLD(such as-but not restricted to- alcohol or drug abuse, medication, chronic hepatitis B or C, autoimmune, etc.);  2. Patients with significantly impaired liver function: ALT or AST≥2 times upper limit of normal;  3. HBsAg(+) and/or HCV-Ab(+), or other liver diseases;  4. Patients with type 1 diabetes mellitus or gestational diabetes or special type diabetes, and patients with BMI＜22Kg/m2;  5. Course of diabetes more than 1 years;  6. Diabetics patients who have taken or are taking oral glucose-lowering drugs or insulin;  7. Diabetics patients with a HbA1c＞7.5% on initial visit;  8. Patients with severe diabetes complications(diabetes ketoacidosis, diabetes coma or with symptomatic of diabetes coma; dysfunction of nerve, retinopathy, dysfunction of kidney);  9. Patients with serum creatinine ≥1.5mg/dL(133umol/L);  10. Patients with a history of cilinically significant heart disease(myocardial infarct, heart failure, and/or severe cardiac rhythm);  11. Complicating severe infection,within 6 months after operation, severe trauma;  12. Patients with excess alcohol consumption≥140g/week(male); ≥70g/week(female);  13. Patients have participated other clinical trials within 24 weeks;  14. Patients with a history of drug allergy to TZDs and berberine;  15. Patients with gestation or possible gestation or lactation, or males or females expecting gestation during clinical trial;  16. Mental diseases patients;  17. Those who refuse to sign informed consent;  18. Any other conditions, which, in the opinion of the investigators would impede compentence or compliance or possiblity of hindering completion of the study;  19. Patients with serum triglyceride≥5.0mmol/L;  20. Patients with thyroid disease, including hyperthyroidism or hypothyroidism. |
| **Randomization:** | The statistical group of Public Health College, Fudan University took responsibility for the preparation and administration of randomization plan. Randomization sequence was generated by SAS8 computer software in a three-center, group randomization manner, and the whole procedure was finished by statistical staff who were not engaged in the study. An envelop randomly labeled with drug assignment was issued only if the database showed that the patient was eligible, had signed the consent statement, and had all required baseline data keyed to the database. The randomization scheme assigned patients to join in one group and accept specific treatment. |
| **Primary Endpoint:** | changes in OGTT (glucose, insulin, AUC of glucose), HbA1c; lipid profile（TC, TG, HDL-c, LDL-c, ApoA, ApoB, ApoE, Lpa); liver enzymes (ALT, AST, γ-GT, ALP). |
| **Study Duration for Each**  **Subject:** | Each subject is followed for 16 weeks; the trial will be completed in 3 year |
| **Number of Centers:** | Three clinical centers in China |
| **Sample Size:** | 180 subjects |
| **Primary Statistical Analysis:** | Statistical analyses will follow the intention-to-treat paradigm, which means that all randomized patients with baseline and 16 week liver enzyme, OGTT, HbA1c,lipid profile and MRS hepatic fat content will be included in the treatment group to which they were assigned. Any randomized patient who does not have the requisite data will be considered unimproved on the primary outcome measure and compared by assigned treatment group. Given the fact that there were two planned primary comparisons, bonferroni-adjusted P values of less than 0.025 were considered to indicate statistical significance. Comparisons of the continuous measures before and after treatment were made with a paired t-test, and the differences from baseline to 16 weeks in BBR plus lifestyle intervention group or PGZ plus lifestyle intervention group were compared with the pure lifestyle intervention group using the analysis of co-variance model respectively, in order to adjust for baseline value. |

1. **STUDY FLOWCHARTS**
   1. **Trial Design**

This study is a three-centers, randomized, open, controlled clinical trial of treatment with pioglitazone, berberine or no drug on the basis of life style intervention for NAFLD patients with IGR or T2DM. The screening period for evaluating eligibility and collecting baseline data lasted up to 4 weeks before randomization. Eligible patients were randomized to receive pioglitazone (15 mg q.d), berberine (0.5g t.i.d.) or no-drug on basis of Life style intervention for 16 weeks. The primary comparison will be made using an intention-to-treat analysis of the change in OGTT (glucose, insulin, AUC of glucose), HbA1c; lipid profile; liver enzymes. The secondary outcome is liver fat content by 1H NMR spectroscopy. A schematic of the trial design is presented in Fig. 1.

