**10.2 Sample Size Estimation**

The planned sample size for the trial was 180 patients with equal allocation to each of the three treatment groups (60 per group). The sample size estimates were based upon a two-group, binomial comparison of the proportions of patients satisfying the decrease in liver fat content over the course of treatment either with pioglitazone or berberine. Since our current study had three treatment groups and two primary hypotheses, the assumption was made that the two primary comparisons, pioglitazone vs. no-drug control and berberine vs. no-drug control, required the type I error estimate be reduced from 0.05 to 0.016 in accordance with three-group comparison. Expected proportions improved were speculated using pilot data from pioglitazone-treat NAFLD studies. There were no available data at the time of study design to estimate liver steatosis response with berberine, which was assumed, for purposes of planning the trial, to be the same as for pioglitazone.

The sample size calculations were performed using the formula: n1=n2=2[(tα+ t2β)s/δ]^2^ with a standard deviation of NAFLD patients liver fat content (s=6.87%, from our prior study), with an expected difference in proportion of improvement between pioglitazone or berberine group and the control group (δ=0.05), with an α level of two-sided type I error (0.016, corrected for three-group comparison), and with a β level of type II error (0.10; i.e., 90% power). The number per group, using the above assumptions was 52. Inflating this number by the 15% expected missing data rate yielded approximately 60 patients per group, or a total of 180 for the trial.

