**10.3 Statistical Analyses**

Statistical analyses for the two primary hypotheses will follow the intention-to-treat paradigm, which means that all randomized patients with baseline and 16 week liver enzyme, OGTT, HbA1c,lipid profile and 1H MRS hepatic fat content will be included in the treatment group to which they were assigned. Missing values will remain missing and patients will be censored at their last follow‐up assessment.

The chi-square test and analysis of covariance or Kruskal-Wallis H test were used to compare baseline variables among the groups for categorical and continuous variables, respectively. Comparisons of the continuous measures before and after treatment were made with the use of a paired t-test, and the differences from baseline to 16 weeks in BBR plus lifestyle intervention group or pioglitazone plus lifestyle intervention group were compared with the lifestyle intervention group using the analysis of co-variance model respectively, in order to adjust for baseline value. Given the fact that there were two planned primary comparisons, bonferroni-adjusted P values of less than 0.025 were considered to indicate statistical significance.

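### Testing each drug against control at a fixed 0.025 is valid, but Holm's step-down would give somewhat more power within the same 5% limit for the two comparisons

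*Protocol*

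**What the plan says.** The primary hypotheses are given in section 10.2 as "the two primary comparisons, pioglitazone vs. no-drug control and berberine vs. no-drug control". For the analysis, the Synopsis and section 10.3 use the same rule: "Given the fact that there were two planned primary comparisons, bonferroni-adjusted P values of less than 0.025 were considered to indicate statistical significance". No step-down, ordering of hypotheses or passing-on of alpha is described, and no reason is given for the single-step form.

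The sample size in section 10.2 rests on a different alpha: "with an α level of two-sided type I error (0.016, corrected for three-group comparison". Its target power is 90%. The inputs are "s=6.87%, from our prior study" and a treatment difference described as "with an expected difference in proportion of improvement between pioglitazone or berberine group and the control group (δ=0.05". No data were available for berberine's effect on steatosis, "which was assumed, for purposes of planning the trial, to be the same as for pioglitazone". The result is 52 per group, raised to 60 for 15% missing data.

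The safety monitoring text in section 4 adds one interim efficacy analysis at about half the data, with O'Brien-Fleming guidelines.

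**The concern.** Once one of the two null hypotheses has been rejected at 0.025, only one is left. It can be tested at 0.05 with the error across the pair still at or below 5%. The fixed rule does not use this. If one drug is clearly positive and the other gives P = 0.03, the second is not significant under the plan but would be under Holm. The trial has two primary hypotheses, so the chance of resolving both matters, most of all for berberine, whose effect was set by assumption.

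**Working it through.** **Inputs** (section 10.2): difference 5 percentage points, SD 6.87 points, equal allocation, 60 per group, 15% missing. Analysis threshold 0.025 (Synopsis, 10.3).

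**The plan's own figure.** With normal quantiles for two-sided 0.016 (2.4089) and 90% power (1.2816):

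n = 2 × [(2.4089 + 1.2816) × 6.87 / 5]² = 51.4, so 52 per group, as stated. Then 52 × 1.15 = 59.8, so 60, also as stated. The figure reproduces only if δ = 0.05 is read as 5 points of liver fat. After 15% loss, 60 × 0.85 = 51 are analysed per arm.

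**Model.** Two z-tests share one control arm of equal size, so their correlation is 0.5. Each has mean θ = δ / [6.87 × √(2/51)] = δ / 1.3605, that is 3.675 for 5 points and 2.205 for 3 points. The critical values are a = 2.2414 (two-sided 0.025) and b = 1.9600 (two-sided 0.05).

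- Bonferroni, drug 1: P(|Z₁| > a).
- Holm, drug 1: P(|Z₁| > a) + P(|Z₁| > b, |Z₂| > a) − P(|Z₁| > a, |Z₂| > a).
- Holm, both drugs: P(|Z₁| > b, |Z₂| > a) + P(|Z₁| > a, |Z₂| > b) − P(|Z₁| > a, |Z₂| > a).

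**Both drugs at 5 points, 51 per arm.** P(|Z| > a) = 0.9242, P(both > a) = 0.8703, and P(one > b, other > a) = 0.8956.

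- Per drug, Holm: 0.9242 + 0.8956 − 0.8703 = 0.9495.
- Both drugs, Holm: 0.8956 + 0.8956 − 0.8703 = 0.9209.
- At least one drug, either rule: 0.9242 + 0.9242 − 0.8703 = 0.9781.

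**Effects of 5 and 3 points (assumed).** Weaker drug, Holm: 0.4855 + 0.5804 − 0.4753 = 0.5906.

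| Assumed true effects (points) | Quantity | Bonferroni | Holm |
|---|---|---|---|
| 5 and 5 | power per drug | 92.4% | 95.0% |
| 5 and 5 | both drugs significant | 87.0% | 92.1% |
| 5 and 5 | at least one significant | 97.8% | 97.8% |
| 5 and 3 | power, weaker drug | about 48.5% | about 59% |
| 5 and 3 | both drugs significant | 47.5% | 58.6% |
| 5 and 0 | power, active drug | 92.4% | 92.6% |
| 5 and 0 | error on the inactive drug | 2.5% | 4.6% |
| 0 and 0 | any false rejection | 4.65% | 4.65% |

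With 52 per arm the first two rows become 92.9% to 95.3% and 87.8% to 92.6%. For 90% power per drug with both drugs at 5 points, 47 per group are needed under Bonferroni and 42 under Holm. Simulation agrees with these values. They ignore the interim look and the baseline adjustment in the covariance model.

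**The case against.** The case for leaving the rule alone is substantial, and most of it stands.

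- **The rule is valid.** A reader might infer that the plan contains a statistical mistake. It does not: 0.05/2 for two comparisons, fixed in advance, controls their joint error.
- **No stated power target is missed.** A reader might infer that the rule leaves the trial underpowered. The trial was sized at 0.016, so testing at 0.025 already gives about 92% to 93% per drug against a 90% target.
- **The loss is not largest under the plan's equal-effects assumption.** That is tempting to infer from section 10.2, but the planning case is among the smaller losses: 5.1 points for showing both drugs, against 11.1 points with effects of 5 and 3.
- **The power is not given up for nothing.** Bonferroni has directly matching 97.5% intervals, and it holds the error on an inactive drug at 2.5% when the other works.
- **The figures are for liver fat**, which the protocol calls secondary. They do not show the gain on glucose, lipids or liver enzymes.
- **The 5% applies to one outcome at a time.** The protocol lists about 16 primary variables (three from the OGTT, HbA1c, eight lipid measures, four enzymes). Neither rule controls error across them, and Holm applied to each adds rejections, some of them false. That is a separate and larger problem.
- **The base alpha is unsettled.** Section 10.2 uses 0.016 and the analysis sections 0.025. The calculation here follows the analysis rule.

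It would also go too far to say that a drug with P between 0.025 and 0.05 is declared ineffective. The protocol defines only statistical significance.

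What the objection does not remove is that Holm rejects everything Bonferroni rejects, and sometimes more, within the same 5% limit for the two comparisons and under any correlation between them.

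**Conclusion.** The point holds as an optional efficiency gain. At the planning effects it is worth about 2.5 points of power per drug and about 5 points for showing both drugs. It adds nothing to the chance of at least one positive result and almost nothing if only one drug works. It reaches about 10 points for the weaker drug under the assumed effects of 5 and 3 points.

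These sizes rest on the liver-fat SD and difference in section 10.2, 51 analysed per arm, normal-theory tests and a correlation of 0.5. That Holm is never less powerful rests on none of these. The gain on the listed primary variables cannot be computed from the protocol.

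**What to change.** In the Synopsis and section 10.3, and in the SAP, replace the fixed threshold as follows. For each primary outcome, compare the smaller of the two unadjusted drug-versus-control P values with 0.025. If it is significant, compare the other with 0.05; otherwise stop.

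Three details belong in the same edit:

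- State that the P values are unadjusted. The present wording could be read as P values already doubled and then compared with 0.025, which would adjust twice.
- Apply the rule within the O'Brien-Fleming boundaries at the interim and final analyses: the boundary for 0.025 first, and the boundary for 0.05 for the remaining drug once the other has been rejected.
- Keep 97.5% intervals for both contrasts, and say that the second drug's interval may include zero when its Holm test is significant.

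The cost is a few sentences and a second set of boundaries, with no extra patients, visits or data. The statistical price is the higher error on an inactive drug when the other works (2.5% to about 4.6%, still under 5%). The change should be fixed before any comparison by arm is seen, including the interim one. It does not replace a decision on the roughly 16 primary variables, or the reconciliation of 0.016 with 0.025.

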**1.2 Schedule of Activities and Assessments**

| Assessment/procedure | **screening（V0）** | **Weeks from randomization** | | | | |
| --- | --- | --- | --- | --- | --- | --- |
|  |  | **V1** | **V2** | **V3** | **V4** | **V5** |
|  | **-4 week** | **0 week** | **4 week** | **8 week** | **12week** | **16week** |
| Consent | ● |  |  |  |  |  |
| Screening questionnaire | ● |  |  |  |  |  |
| Baseline medical history | ● |  |  |  |  |  |
| Follow up medical history | ● | ● | ● | ● | ● | ● |
| Inclusion/exclusion criteria | ● | ● |  |  |  |  |
| Randomization |  | ● |  |  |  |  |
| Health education & diet guide |  | ● | ● | ● | ● | ● |
| Review of concomitant drugs |  |  | ● | ● | ● | ● |
| Review for adverse effects |  |  | ● | ● | ● | ● |
| Drug dispensing |  | ● | ● | ● | ● |  |
| Review of drug adherence |  |  | ● | ● | ● | ● |
| Nutrition questionnaire |  | ● |  |  |  | ● |
| Activity questionnaire |  | ● |  |  |  | ● |
| Physical exam (Detailed/Focused) | D | F | F | F | F | D |
| OGTT with insulin |  | ● |  |  |  | ● |
| Fasting glucose/2h after meal | ● |  | ● | ● | ● |  |
| Fasting lipid profile | ● | ● |  |  |  | ● |
| Liver and renal fuction | ● | ● | ● | ● | ● | ● |
| Blood and urine routine |  | ● | ● | ● | ● | ● |
| HbA1c | ● |  |  |  |  | ● |
| Pregnancy test (females) |  | ● |  |  |  | ● |
| Serum, plasma for banking | ● | ● | ● | ● | ● | ● |
| Hepatic virus anti-body（HBsAb、HCV-Ab） | ● |  |  |  |  |  |
| ECG | ● |  |  |  |  | ● |
| Liver fat content（MRS） | ● | ● |  |  |  | ● |

**2. Background and Rational**

**2.1 The burden of non-alcoholic fatty liver disease and associated metabolic disorders in China**

The global NAFLD prevalence was approximately 20% in 2005 [1,2], and this ratio might increase rapidly with the improvement of human living standard and changes of dietary structure. NAFLD has presented serious threats to human health, not only due to direct damage to hepatocytes, but also hepatic metabolic disorders associated with diabetes and cardiovascular disease(CVD). It was reported that one third of NAFLD patients suffered from metabolic syndrome(MS)[3], and OGTT test showed that 44% NAFLD patients without diabetes history before were abnormal in carbohydrate metabolism, including 13% IGT(impaired glucose tolerance) and 33%DM(diabetes mellitus)[4]. In addition, several studies also showed that NAFLD was an independent risk factor for type 2 diabetes and CVD, and elevation of hepatic enzymes, such as ALT, AST and γ-GT, could increase risks of DM and CVD in people from different ethnic groups [5-12]. To interfere with NAFLD at an early stage had significant benefits to alter its natural history and outcome leading to DM and CVD.

**2.2 Pathogenesis and potential treatments of NAFLD**

Non-alcoholic fatty liver disease (NAFLD) is a common and increasingly recognized liver disease characterized by the accumulation of fat in at least 5% of hepatocytes. The mechanisms underlying NAFLD pathogenesis remain unclear, but prior studies reported that NAFLD was associated with obesity, insulin resistance, dyslipidemia, oxidative stress and abnormal cytokine[13-17]. Histologically, NAFLD can be divided into simple steatosis (non-alcoholic fatty liver: NAFL), non-alcoholic steatohepatitis (NASH) and end-stage liver cirrhosis. Several agents have been found promising as therapy of NAFLD in small clinical trials, but none was approved for general use at present[18-21].

There were no definite therapies for NAFLD currently, due to the uncertainty of its pathogenesis. Lifestyle improvement is a recommended choice, but most patients are unable or unwilling to undertake strict lifestyle control. Anti-obesity drugs (orlistat, rimonabant), antioxidants (vitamin C and E), cytoprotective agents (UDCA), lipid-regulating agents, insulin sensitizers, as well as traditional Chinese medicine have been reported to have beneficial effects on NAFLD.

Several recent pilot studies have shown encouraging results using the insulin sensitizing thiazolidinediones (TZD) to treat NAFLD in non-diabetic individuals [22-25]. Because these studies have had small sample sizes, lacked control groups, or had short follow-up, the reliability of TZD effects on NAFLD still need further evidence from large-scale, randomized, and controlled prospective clinical trial.

Recently, Berberine(BBR) a compound isolated from a Chinese herb, was found to lower serum cholesterol by up-regulating the expression of LDL receptors [26]. Several studies have showed BBR’s potential to correct NAFLD patients’ metabolic disorders and mitigate liver steatosis. However, these studies enrolled only small number of patients and were not placebo-controlled. Furthermore, it was not accurate enough to use ultrasound to evaluate hepatic fat content[27,28].

**3. Study Objective**

**3.1 Primary**

The primary objective of the randomized, three-centers, open, controlled trial is to determine whether pioglitazone or berberine plus lifestyle intervention was superior to pure lifestyle intervention on reducing blood glucose (OGTT glucose, insulin, AUC of glucose and HbA1c), lipid profile（TC, TG, HDL-c, LDL-c, ApoA, ApoB, ApoE, Lpa) and liver enzymes (ALT, AST, γ-GT, ALP) in NAFLD patients with abnormal glucose metabolism.

**3.2 Secondary**

To assess the secondary composite outcomes from the following perspectives:

- Efficacy:
  - Changes in body weight after 16 weeks of treatment.
  - Changes in hepatic fat content by 1H MRS after 16 weeks of treatment (total cholesterol, triglyceride, HDL-C, LDL-C,Apo-A, Apo-B, Apo-E and Lpa) from baseline.
- Safety:
  - Incidence of adverse events.
  - Changes in laboratory parameters (hematology, biochemistry) and vital signs after treatment.

**4. Study design and management overview**

**4.1 Study Design Overview**

The study is a three-centers, randomized, open, controlled clinical trial of treatment with pioglitazone, berberine or no drug on the basis of life style intervention for NAFLD patients with IGR or T2DM. The screening period for evaluating eligibility and collecting baseline data lasted up to 4 weeks before randomization. Eligible patients were randomized to receive pioglitazone (15 mg q.d), berberine (0.5g t.i.d.) or no-drug on basis of Life style intervention for 16 weeks. The primary comparison will be made using an intention-to-treat analysis of the change in OGTT (glucose, insulin, AUC of glucose), HbA1c; lipid profile（TC, TG, HDL-c, LDL-c, ApoA, ApoB, ApoE, Lpa); liver enzymes (ALT, AST, γ-GT, ALP). The secondary outcome is liver fat content by 1H NMR spectroscopy.

